# SUMMARY OF RESEARCH

**TITLE: Human consumption of fermented millet (*Kunun zaki*) reduces the prevalence of selected antimicrobial resistance genes in human fecal samples**

**BACKGROUND:** The gut microbiota is home to more than 500 philotypes or approximately 1 million bacterial genes. It provides a secondary barrier against pathogenic colonisation. It is also host to neurons hormones and secondary messengers (largest neuroendocrine organ in the body) and therefore regulates many physiological functions. In the same way a dysbiosis of the gut microbiota could result in proliferation of pathogenic strains of bacteria and impair the physiologic functions of the body, it could also be deliberately modulated to achieve beneficial effects through competitive exclusion. This has been demonstrated in many researches just as whole cereal grain have been shown to have potential health effects.

The gut microbiota serves as a reservoir for antimicrobial resistance genes (ARGs), which can be transferred between commensal and pathogenic bacteria. Understanding how dietary interventions, particularly traditional fermented beverages, modulate the gut resistome is crucial for developing strategies to reduce antimicrobial resistance burden in communities.

**Study Population and Sample Collection**

A total of 36 healthy human volunteers (males and females), aged between 3 and 65 years and residing in Abuja, North Central Nigeria, will be recruited for this study. Eligible participants will enter a two-week monitoring phase to ensure compliance with exclusion criteria, verified through a daily online 24-hour food and drug recall questionnaire. Participants will then be assigned to Kunun aya, Kunun zaki, or control group (no intervention) by chance as they come, with 12 participants per group. Participants will supplement their habitual diet with 500 mL daily of the assigned beverage for two weeks, followed by a two-week washout phase.

Fecal samples will be self-collected by participants across three phases: prior to beverage consumption (baseline), after two weeks of beverage consumption, and at two weeks post-intervention (washout phase). Samples will be prepared according to the method described by Nsubuga et al. (2004). DNA will be extracted from fecal samples using the DNA Stool Mini Kit (Qiagen, USA) according to the manufacturer's instructions and stored at −20°C.

**Expected Outcome:** At the end of this research it is expected that there will be significant changes in the gut resistome composition of participants following consumption of the local drinks. Specifically, we expect to observe changes in the abundance and diversity of antimicrobial resistance genes, with potential decreases in clinically relevant ARG classes through competitive exclusion mechanisms and modulation of the gut microbial community structure.

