## Primary and Secondary Outcomes

### Primary Outcome

The primary outcome is the change in gut resistome composition, measured as the difference in total antimicrobial resistance gene (ARG) abundance and diversity between baseline and post-intervention timepoints (2 weeks). This will be quantified using ARG detection by PCR, with results analyzed at the conclusion of the 2-week intervention period. The primary endpoint compares ARG profiles between the intervention groups (Kunun Zaki and Kunun Aya) and the control group using permutational ANOVA (PERMANOVA) with alpha set at 0.05.

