**Research Design**

This is a human intervention study with three arms (1:1:1 allocation ratio) designed to assess superiority of two fermented beverage interventions (Kunun Zaki and Kunun Aya) compared to a control group (no intervention) in modulating the gut resistome. The research follows a quasi-experimental design with participants assigned to different groups by chance to receive either *Kunun Zaki, Kunun Aya*, or no intervention for a 2-week period, followed by a 2-week washout phase. Sample collection occurs at baseline (pre-intervention), at the end of the 2-week intervention period, and at the end of the 2-week washout period.

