**Study population**

A total of 36 persons will be selected for this study (12 per group).

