### Eligibility Criteria

### Inclusion criteria

Healthy individuals aged between 3 and 65 years, good general health, and a signed consent form (or assent with parental consent for minors).

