**Sample Size**

A sample size of 36 participants (12 per group) was determined based on feasibility considerations and previous microbiome intervention studies.

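### Assignment by chance on arrival, under a quasi-experimental label, does not define an unpredictable 1:1:1 allocation for a superiority comparison

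*Protocol*

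**What the plan says.** The allocation rule appears twice in the protocol.

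- Summary, Study Population and Sample Collection: after the two-week monitoring phase, participants go to one of the two beverages or to the "control group (no intervention) by chance as they come, with 12 participants per group".
- Research Design: "The research follows a quasi-experimental design with participants assigned to different groups by chance". The same paragraph opens: "This is a human intervention study with three arms (1:1:1 allocation ratio) designed to assess superiority".

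The Study population section repeats the numbers: "A total of 36 persons will be selected for this study (12 per group". The Sample Size section says that the total "was determined based on feasibility considerations and previous microbiome intervention studies". The Primary Outcome section compares the beverage groups with "the control group using permutational ANOVA (PERMANOVA) with alpha set at 0.05". The Inclusion criteria admit "Healthy individuals aged between 3 and 65 years, good general health".

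The protocol does not describe a random sequence, blocks, strata, concealment or the person who assigns. It never calls this trial randomised; that word is used only for cited studies.

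**The concern.** The protocol asks for three things together: chance assignment as people arrive, exactly 12 per arm, and a comparison strong enough to claim superiority. The first two can be combined in several ways, and the text does not say which. The third requires that nobody enrolling participants can foresee the next assignment. The quasi-experimental label adds a conflict, because it normally signals that allocation was not random.

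Concealment matters here because the control drinks nothing, so participants and the staff who deliver the beverages know the arm once it is given. Concealment before assignment is then the main protection left against selective enrolment. The PERMANOVA p-value also comes from exchanging group labels between people. Random allocation is what justifies that exchange; a foreseeable rule weakens it.

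This is not a matter to leave to an analysis plan. Allocation is a design rule that the protocol does state, and a later document cannot repair an allocation already carried out.

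**Working it through.** **Inputs.** From the protocol: three arms, 1:1:1, 12 per arm, alpha 0.05. The total reproduces: 3 × 12 = 36. There is no power calculation to reproduce.

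**Reading A: each arrival is assigned independently with probability 1/3.**

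- P(12/12/12) = 36! / (12!³ × 3³⁶) = 0.0226, or 2.3%.
- Summing the same multinomial over all splits gives P(smallest arm ≤ 9) = 0.54 and P(smallest arm ≤ 8) = 0.31.

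The assignments are unpredictable, but the stated group size is usually missed.

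**Reading B: equal chance among the open arms, each arm closed at 12.** The split is always met. In 100,000 simulated trials:

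- Assignments made when only one arm was open (fully determined): mean 3.2, 5th to 95th percentile 1 to 7.
- Assignments made with at least one arm closed: mean 8.4, 5th to 95th percentile 3 to 15.

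So of 36 assignments, about 3 can be known for certain and about 8 can be narrowed by anyone who sees the running counts.

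**Reading C: 36 lots, 12 per arm, drawn without replacement.** The split is again always met. The identity used is Σₖ≥₁ C(m,k)/C(n,k) = m/(n − m + 1).

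- Expected number fully determined at the end: 3 × 12/(36 − 12 + 1) = 36/25 = 1.44.
- Expected number with at least one arm exhausted: 3 × 24/(36 − 24 + 1) − 36/25 = 5.54 − 1.44 = 4.10.

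**Reading D: rotation through the arms in order of arrival.** Every assignment would be foreseeable. The words by chance argue against this reading, and it is listed only because the rule is not otherwise defined.

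| Reading | 12/12/12 | Mean fully determined | Mean with an arm closed |
|---|---|---|---|
| A, unrestricted | 2.3% | 0 | 0 |
| B, arms closed at 12 | always | 3.2 | 8.4 |
| C, lots | always | 1.44 | 4.10 |
| D, rotation | always | 36 | not applicable |

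**What a distortion could do (illustration only).** Assume a continuous outcome, 12 v 12, a two-sided normal test at 0.05, no true effect, and a prognostic shift of d SD between arms. The standard error is √(2/12) = 0.408 SD. The rejection rate is Φ(d/0.408 − 1.96) + Φ(−d/0.408 − 1.96):

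- d = 0.25: 9.4%
- d = 0.5: 23%
- d = 0.75: 45%

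The documents give no SD or effect size. These shifts are assumptions, and nothing shows that the allocation would produce them.

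**The case against.** The strongest reply is that 12 per group and 1:1:1 are fixed in three places, so chance assignment is already restricted. Drawing 12 lots per arm as people arrive fits the text and secures the split. That stands: the 2.3% and 54% describe Reading A only, and they do not show that 12/12/12 is out of reach. A reader might infer that the split cannot be relied on; the documents do not support that.

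It is also true that any scheme with fixed totals determines its last assignment, and that an unconcealed blocked list is foreseeable at the end of each block. So restriction alone is not the fault. What is missing is a stated generation method together with concealment. That no list exists is an inference from none being described.

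Three further inferences are tempting and go beyond the text.

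- **That staff or participants choose the arm.** The protocol says by chance and permits no choice. Steering is a risk that concealment would remove, not a stated practice.
- **That relatives arrive together and share an arm.** No section mentions household recruitment.
- **That the age range of 3 to 65 proves the allocation faulty.** Age imbalance can arise under perfect randomisation with 12 per arm. It bears on stratification, not on this rule.

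Finally, the primary outcome is a change from baseline, which partly removes stable differences between people. That limits the illustrative rejection rates, but it does not remove differences in how people would change over two weeks.

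**Conclusion.** The concern holds as an undefined allocation rule paired with a conflicting design label. Depending on the reading, the wording either leaves the 12/12/12 split to a 2.3% chance, or secures it with a number of late assignments open to foresight: on average about 3 fully determined and 8 with an arm closed under capping, about 1.4 and 4 under lots. Those averages assume equal chances among open arms or a full lot draw, and they matter only if the person enrolling can see the counts.

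A reader might also infer that the quasi-experimental label by itself rules out a causal claim. It does not: the procedure decides what can be concluded, and the label needs to match the procedure. As written, neither the procedure nor the label supports superiority against an unblinded no-beverage control. This must be fixed before the first assignment, because it cannot be reliably repaired afterwards.

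**What to change.** Replace the allocation wording in both the summary and Research Design with one rule:

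- a computer-generated 1:1:1 permuted-block list, with varying block sizes that are multiples of 3 and sum to 36 (for example 3, 3, 6, 6, 9 and 9 in random order), which gives exactly 12/12/12;
- prepared by someone who does not enrol participants;
- concealed in sealed sequential envelopes or a web form;
- opened only once the participant has passed the run-in and handed in the baseline sample. The summary already places assignment after the run-in, but does not say whether the baseline sample comes first.

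Then call the design randomised in Research Design.

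If this is not done, keep the quasi-experimental label, drop the causal superiority wording, and adjust the comparison for baseline resistance-gene status and age.

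Stratifying by age band is optional, and exact 12/12/12 is then not guaranteed. For example, assume 10 children and 26 adults in blocks of 3. That gives 3 + 8 = 11 complete blocks, hence 11 per arm, with one child and two adults left in incomplete blocks. Those three fall 1/1/1 with probability only 1/3.

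The cost is about an hour to make the list, some protocol wording and minor handling. The sample size stays at 36.

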**Protocol and Statistical Analysis Plan Access**

The full research protocol and statistical analysis plan will be made publicly available through the research registry and the institutional repository of the University of Ibadan upon completion of ethics approval. Additional materials may be obtained by contacting the principal investigator at the Department of Environmental and Occupational Health, School of Public Health, Indian University

# Data Sharing Statement

The datasets generated and analyzed during the current study are available from the corresponding author upon reasonable request. De-identified participant data, the data dictionary, and statistical code will be shared following approval of a proposal and with a signed data access agreement.

# Funding and Conflicts of Interests

## Funding Sources

No funding sources are reported for this research

## Conflicts of Interest

The authors declare no financial or other conflicts of interest related to this research.

# **INTRODUCTION**

**Background of the Study**

In recent years, there has been increased focus by researchers on the composition and relative abundance of the gut Microbiota. With improving technologies that allow whole genome sequencing, metagenomics analysis of the gut microbiota has revealed better insights and holds promising future for the field of Microbiology and Medicine. The gut Microbiota is a rich flora of bacteria that naturally inhabit the gut playing significant role in metabolism among many other functions (Cani 2018). Because of their inter-relationship with different human cell, changes in their composition and distribution have been linked to potential diseases and even disease symptoms (Cani 2018).

The gut microbiota is home to more more than 500 philotypes or approximately 1 million bacterial genes (Jiang et al 2013). The gut microbiota not only provides a secondary barrier against pathogenic colonisation but is also a host to neurons hormones and secondary messengers (largest neuroendocrine organ in the body) and therefore regulates many physiological functions (Neuman et al 2015). It also produces Metabolites like SFA, provides energy to epithelial cells of intestine and prevents the expression of virulence factors (Rinttila and Apajalahti 2013)

In the same way a dysbiosis of the gut microbiota could result in proliferation of pathogenic strains of bacteria and impair the physiologic functions of the body, it could also be deliberately modulated to achieve beneficial effects through competitive exclusion. This has been achieved in the case of newly hatched chicks prevented from Salmonella enteritidis infection through administration of suspension of intestinal contents of healthy chickens to the chicks in doses (Kogut 2019). Gargari et al (2016) investigated gut microbiota modulation through the consumption of a Bifidobacterium bifidum strain for 4 weeks and found that the dominant intestinal bacterial taxa and fecal butyrate in healthy adults were modulated. While attempts to modulate the gut microbiota usually focuses on direct repopulation of gut microbiota with beneficial organisms, there have been also indications that certain food substances provide nutrients that help in developing and maintaining a healthy gut microbiota population. For instance, whole cereal grain are said to have potential health effects (Gong et al 2018). In a 6 week randomized research, adults who consumed whole grains had their gut microbiota as well as immune and inflammatory markers positively impacted (Vanegas et al, 2017). In a 4 weeks randomized cross over research, healthy humans who consumed whole grains of barley and brown rice, lead to an increase in microbial diversity (Martinez et al, 2013).

The gut microbiota also serves as a major reservoir for antimicrobial resistance genes (ARGs). These genes can be transferred horizontally between commensal and pathogenic bacteria, contributing to the spread of antimicrobial resistance. The gut resistome encompasses all resistance genes present in the gut microbiota, including those conferring resistance to clinically important antibiotics such as beta-lactams, macrolides, tetracyclines, and aminoglycosides. Dietary interventions that modulate gut microbial composition may consequently affect the abundance and diversity of resistance genes in the gut ecosystem.

### Rationale for the Study

Kunu contains beneficial bacteria as well as blended cereal (fibre) which makes it suitable to serve both as a probiotic through gut microbiota modulation, and prebiotic by stimulating the growth of other bacteria. The fermentation process in Kunun production involves lactic acid bacteria which may competitively exclude potential pathogenic bacteria and their associated resistance genes. Understanding how traditional fermented beverages affect the gut resistome is important for public health, particularly in regions where antimicrobial resistance is a growing concern and where these beverages are regularly consumed.

### **Objective of the study**

The general objective of this research is to study possible gut resistome changes due to consumption of local drinks for a period of two weeks, comparing gut resistome profile before, during and after the period through:

1. Analysis and comparison of gut resistome changes in participants after consumption of Kunu zaki and Kunu aya for a period of two weeks.

2. Study specific antimicrobial resistance gene signatures that may appear or disappear after Kunu consumption.

3. Evaluate changes in the abundance and diversity of clinically relevant resistance genes following consumption of Kunu Zaki and Kunu Aya for two weeks.

## Primary and Secondary Outcomes

### Primary Outcome

The primary outcome is the change in gut resistome composition, measured as the difference in total antimicrobial resistance gene (ARG) abundance and diversity between baseline and post-intervention timepoints (2 weeks). This will be quantified using ARG detection by PCR, with results analyzed at the conclusion of the 2-week intervention period. The primary endpoint compares ARG profiles between the intervention groups (Kunun Zaki and Kunun Aya) and the control group using permutational ANOVA (PERMANOVA) with alpha set at 0.05.

### Secondary Outcomes

1. Prevalence changes of specific ARG classes (beta-lactam, macrolide, tetracycline, aminoglycoside resistance genes) measured at baseline, 2-week post-intervention, and 2-week washout periods.

2. Persistence of resistome changes during the washout phase (measured at 2 weeks post-intervention cessation) compared to baseline and intervention periods.

3. Identification of specific ARG signatures that appear or disappear following consumption of each fermented beverage.

4. Safety outcomes including participant-reported gastrointestinal symptoms and adverse events throughout the study duration.

# METHODS

**Patient and Public Involvement**

Patients and members of the public were not involved in the design, conduct, or reporting plans for this research. However, participants will be informed of the study results upon completion through a summary report and will have the opportunity to receive their individual resistome profile results if they express interest.

**Research Design**

This is a human intervention study with three arms (1:1:1 allocation ratio) designed to assess superiority of two fermented beverage interventions (Kunun Zaki and Kunun Aya) compared to a control group (no intervention) in modulating the gut resistome. The research follows a quasi-experimental design with participants assigned to different groups by chance to receive either *Kunun Zaki, Kunun Aya*, or no intervention for a 2-week period, followed by a 2-week washout phase. Sample collection occurs at baseline (pre-intervention), at the end of the 2-week intervention period, and at the end of the 2-week washout period.

**Research Setting**

Study site: All samples will be collected from residents of Abuja, North Central Nigeria. All laboratory analysis will be carried out in [name] Laboratory at the Department of Environmental and Occupational Health, School of Public Health, Indiana University.

**Study population**

A total of 36 persons will be selected for this study (12 per group).

### Eligibility Criteria

### Inclusion criteria

Healthy individuals aged between 3 and 65 years, good general health, and a signed consent form (or assent with parental consent for minors).

### Exclusion criteria

Engaging in any of these during 2 weeks prior to the first sample collection; antibiotic use, intentional intake of probiotic or prebiotic products, presence of gastrointestinal disorders such as diarrhea, inflammatory bowel disease, or irritable bowel syndrome, pregnancy or breastfeeding, alcoholism and drug addiction. For the entire 6 weeks this research will last for, participants will be required to report their daily food and drug intake using an individualised web app developed for this purpose.

Interventions and Comparator

**Intervention 1 - Kunun Zaki:** Participants will consume 500 mL of Kunun Zaki daily for 2 weeks. Kunun Zaki is a traditional Nigerian fermented beverage made from millet or sorghum, supplemented with ginger and cloves as spices.

**Intervention 2 - Kunun Aya:** Participants will consume 500 mL of Kunun Aya daily for 2 weeks. Kunun Aya is a traditional Nigerian fermented beverage made from tiger nuts, prepared through similar fermentation processes as Kunun Zaki.

**Control:** Participants in the control group will maintain their habitual diet without any intervention beverage for the 2-week period.

All participants will be instructed to maintain their usual dietary habits aside from the intervention beverage. Interventions will be delivered by study personnel who will ensure participants receive fresh beverages daily. Adherence will be monitored through daily self-reported logs via the web-based food diary.

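### Antibiotic use before the two-week run-in is not restricted and, as far as the protocol shows, not recorded, so within-arm resistance-gene changes may include recovery drift and balance between arms cannot be checked

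*Protocol*

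**What the plan says.** - **Antibiotic window.** Protocol, Exclusion criteria: "during 2 weeks prior to the first sample collection; antibiotic use" is the first of the listed exclusions. No earlier period is mentioned.
- **Run-in.** Protocol, Study Population and Sample Collection: "Eligible participants will enter a two-week monitoring phase to ensure compliance with exclusion criteria". It covers the same two weeks as the antibiotic window.
- **Diary.** Protocol, Exclusion criteria: food and drug intake is reported daily "For the entire 6 weeks this research will last for".
- **Rest of the timeline.** Protocol, Research Design: assigned groups are followed "for a 2-week period, followed by a 2-week washout phase".
- **First contact.** Protocol, Frequency of interviews, describes an initial questionnaire on suitability. Its questions are not shown.
- **Primary comparison.** Protocol, Primary Outcome: it "compares ARG profiles between the intervention groups (Kunun Zaki and Kunun Aya) and the control group". The control condition is concurrent: "Participants in the control group will maintain their habitual diet without any intervention beverage for the 2-week period".
- **Readouts over time.** Secondary outcome 2 is "Persistence of resistome changes during the washout phase (measured at 2 weeks post-intervention cessation) compared to baseline and intervention periods". Secondary outcome 3 looks for gene signatures that turn up or vanish after each drink. The Objective of the study compares profiles over the successive periods, and the Statistical methods section plans comparisons over time as well as between groups. None of the over-time items states that change is to be taken relative to control.
- **Allocation.** Twelve per group, by chance in order of arrival, in a design that the protocol calls quasi-experimental.

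**The concern.** Antibiotics act directly on the genes being measured, and by excluding recent use the protocol accepts that they disturb the outcome. A participant whose course ended 15 days before the first sample is nevertheless eligible. If that participant's gut flora is still recovering, the baseline sample is a point on a moving curve, and the week-2 and washout samples lie further along it.

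Within one arm, such movement cannot be told apart from an effect of the drink. A fall at week 2 that remains at washout is what secondary outcome 2 would describe as a persistent change, and a gene lost during recovery would count as a vanished signature under secondary outcome 3. The title and the expected outcome already point towards reductions.

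The primary comparison has a control arm, but each arm is small and the allocation method is described only loosely. Without the date of the last course, nobody can tell afterwards whether recent users were spread evenly. The information is hard to recover reliably once the trial is over.

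**Working it through.** **1. What the records cover.** Run-in 2 weeks + beverage 2 weeks + washout 2 weeks = 6 weeks, which matches the stated duration. The diary therefore starts with the run-in, and neither the exclusion rule nor the diary reaches further back. The group sizes also agree: 3 × 12 = 36. The sample size rests on feasibility, so there is no power calculation to reproduce.

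**2. Assumptions, none from the documents.** A share q of participants took antibiotics shortly before the two-week window. Their change from baseline drifts by D standard deviations (SD of change in everyone else). The beverage has no effect; tests are two-sided at 0.05; n = 12 per arm; 40,000 simulated trials. A t-test on a continuous change score stands in for the planned PERMANOVA and prevalence analyses, so the results show order of magnitude only.

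**3. Expected within-arm drift and noise.** Mean drift = q × D. Variance of change = 1 + D² × q × (1 − q).
- q = 0.10, D = 1: drift 0.10 SD; variance 1 + 0.09 = 1.09.
- q = 0.20, D = 1: drift 0.20 SD; variance 1 + 0.16 = 1.16.
- q = 0.20, D = 2: drift 0.40 SD; variance 1 + 4 × 0.16 = 1.64, so 12 participants carry about the information of 12 / 1.64 = 7.3.

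**4. Simulated false-positive rates.**

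| Recent users | Drift | Before/after, one arm | Beverage vs control |
|---|---|---|---|
| 10% | 1 SD | 5.8% | 5.0% |
| 10% | 2 SD | 7.0% | 4.9% |
| 20% | 1 SD | 8.8% | 5.1% |
| 20% | 2 SD | 14.5% | 4.9% |
| 30% | 1 SD | 13.2% | 5.0% |
| 30% | 2 SD | 26.6% | 5.0% |
| 40% | 1 SD | 19.9% | 5.0% |
| 40% | 2 SD | 42.0% | 5.1% |

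The simulation error at 5% is √(0.05 × 0.95 / 40,000) = 0.1 percentage point, so the last column does not differ from 5%. The mean between-arm bias was about 0 throughout.

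**5. Balance between arms.** Under chance allocation, two arms of 12 differ by three or more recent users with probability 8% (q = 0.10), 20% (0.20), 26% (0.30) or 30% (0.40). The 5% error rate already allows for this. If allocation were not random and one beverage arm had 25 percentage points more recent users, the between-arm false-positive rate would be about 8-9% for a 1 SD drift and 14-15% for 2 SD.

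**The case against.** **The concurrent control deals with it.** All arms share the same window and sampling times, so recovery acts on them alike on average. This stands for the primary comparison: a reader might infer that no planned analysis can remove the drift, but the between-group contrast removes it in expectation. What remains there is added noise. The rise to 8-15% needs a failure of allocation, which the short look-back does not cause; the missing date only prevents a check.

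**There is no contradiction.** A reader might infer that the protocol contradicts itself by leaving two-week persistence of a drink's effect open while treating two weeks as enough after antibiotics. The documents do not support that. They never claim that two weeks gives a settled baseline; the run-in serves to check eligibility. An open question about a food effect says nothing about how long antibiotic recovery takes.

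**Unequal counts are not bias.** With 10% recent users, two arms of 12 have unequal numbers with probability 72%. That sounds alarming, but for a trait present in half the population the figure is about 84%. It shows that the arms are small.

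**Size and direction are unknown.** The documents give no exposure rate and no recovery time, and they do not say that carriage falls during recovery. Conventional PCR may stay positive through a partial decline. This stands, and it is why the rates above are conditional and why no particular longer window can be derived from the documents.

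**It may already be covered.** The first-contact questionnaire might ask about earlier courses, and an analysis plan that is not shown might hold a sensitivity analysis. That is possible. But the protocol defines suitability by the two-week rule and mentions no earlier history, and an analysis plan cannot use a date that was not collected.

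**Conclusion.** The point holds in a limited form and is a low-cost improvement. Antibiotic use before the run-in is unrestricted, and the protocol describes no record of it. The primary beverage-versus-control comparison is not biased on average under chance allocation; it loses some precision. The exposed readouts are those over time without a stated control: the general objective, secondary outcomes 2 and 3, and the over-time comparisons in the statistical methods. There the before/after false-positive rate is about 6% with 10% recent users and 1 SD drift, and 9-15% with 20% recent users and 1-2 SD drift. The 42% extreme needs 40% recent users and a 2 SD drift, and should not be quoted as typical. All these figures rest on assumed exposure and drift and on a t-test stand-in for the planned analyses. Separately, with order-of-arrival allocation in a design labelled quasi-experimental, imbalance in recent users could not be checked from what the protocol says is collected.

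**What to change.** 1. At the existing first-contact questionnaire, record the date of the last antibiotic course, or that none is recalled.
2. Report time since the last course by arm alongside the other baseline data.
3. Repeat the primary and prevalence comparisons without participants who had a recent course. The sponsor should define recent in advance and justify the window; the documents support no particular length. If recruitment allows, the same window could become the exclusion rule, with the two-week run-in kept for daily verification.
4. State that beverage conclusions, including persistence at washout and signatures that turn up or vanish, rest on change relative to control. Within-arm change alone would be descriptive.

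The cost is one extra question, one sensitivity analysis and a sentence in the analysis section. Recall of dates will be imperfect, and the sensitivity analysis will leave fewer than 12 in an arm wherever recent users are removed. Nobody is turned away unless the optional longer exclusion is adopted, which would defer or lose some volunteers in a trial sized on feasibility.
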